### Sample Size and Randomization

To calculate the sample size, the 2 objectives that require such calculation are considered:

For the patient satisfaction surveys, proposed on a Likert scale from 1 to 5, we are faced with the problem of comparing independent samples. Assuming normality in the difference of the samples (a hypothesis that will be verified during the statistical tests), the formula for the determination of the required sample size is the following:

Where Z_α_ and Z_β_ represent the Z-table values for confidence level and test power, respectively, sigma is the SD of the (estimated) differences, and d is the effect size to be measured. For this study, standard values for α=.05 (95% confidence) and β=.8 (80% test strength) are selected, σ=1 is estimated as an extreme case to ensure that the results will be statistically significant, and d=0.25, as the minimum improvement we want to demonstrate. The result is n=395.21 for each group, so we set the number of patients to be analyzed to 400 with the AI-powered tool and 400 without the tool.For time-saving, applying a similar procedure with the same standard values, σ=90 seconds and d=30 seconds, we obtain n=111.15 for each group, so we set the number of consultations to be analyzed to 120 with the AI-powered tool and 120 without the tool.Since the groups are the same and there is no interconnection between the measurement of both objectives, it is possible to use the same consultations for both, and therefore the total number of patients required will be the larger of the two above, resulting in n=800 (400 patients with the AI-powered tool and 400 without the tool).The randomization was carried out in a simple format, given the sufficient sample size and the fact that the aim is to validate the hypotheses at a general level, although for information purposes the study also shows intermediate results stratified by type of consultation (first or follow-up) or by a health professional.

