**Dependent variables**
Results for each survey question, on a scale of 1-5.Time saved during consultations is measured by comparing the writing time in the 2 scenarios: one where doctors manually write notes during the consultation (non–AI-powered audios) and another where they review and correct notes generated by the AI-powered tool. For the non–AI-powered audios, investigators listen to the recordings and measure the exact time the professional spends writing. In AI-assisted consultations, the doctors use the platform to time their note corrections. By comparing these two measurements, the study aims to quantify the time-savings offered by the AI-powered tool, with each recording being analyzed individually for accuracy. This has been chosen because other forms of measurement (such as automatically measuring silences) may introduce greater biases (silences due to circumstances other than note taking) than human interpretation. Although logically it is not a perfect measure either, the savings impact is expected to be sufficiently significant for these random errors to have a very small impact in relative terms.In addition, health care professionals are asked to include, through the AI-powered tool’s digital platform, possibly relevant comments about the consultation they have just carried out, such as when a consultation has been carried out in multiple languages, with one participant speaking in Spanish and another in Catalan.

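### The plan does not say whether 120 consultations per group is a minimum or the number analysed for time, and the 120 rests on an unstated one-sided test (about 73% power if two-sided)

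*Protocol article*

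**What the plan says.** All references are to the Protocol article.

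- **Sample Size and Randomization, general inputs.** "standard values for α=.05 (95% confidence) and β=.8 (80% test strength) are selected" (the .8 is evidently the power). Whether the test is one- or two-sided is not stated.
- **Sample Size and Randomization, time saving.** "σ=90 seconds and d=30 seconds, we obtain n=111.15 for each group", and on that basis "we set the number of consultations to be analyzed to 120 with the AI-powered tool and 120 without the tool".
- **Same section, next sentence.** "it is possible to use the same consultations for both, and therefore the total number of patients required will be the larger of the two", "resulting in n=800 (400 patients with the AI-powered tool and 400 without the tool"). The 120 is neither withdrawn nor described as a minimum.
- **Textbox 1, Dependent variables.** For control consultations, investigators obtain the typing time by listening to the audio. "In AI-assisted consultations, the doctors use the platform to time their note corrections". The description ends "with each recording being analyzed individually for accuracy" and repeats no limit of 120.
- **Overview, Design, and Hypotheses of Study (workflow steps).** Every control consultation is recorded so that typing time can be calculated. Logging the review time on the platform is part of each AI consultation.
- **Statistical Analysis.** Time saving is one of the two main hypotheses. It is to be compared as relative time in percent, by a t test or a nonparametric equivalent, at 95% confidence. Sidedness is again not given.

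**The concern.** Two things are left open for a main hypothesis.

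First, the number analysed. The sample size section gives 120 per group as the number of consultations to analyse, out of 400 per group collected. Read literally, 280 of 400 consultations in each arm would not enter the time comparison. In the AI arm those review times would already have been logged. No rule says which 120 would be used. Control recordings not timed before the end of the study could not be timed later, because Data Collection says that recordings are then deleted.

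Second, the basis of the 120. If the test is two-sided, as 95% confidence is usually understood, 120 per group does not reach the 80% power that the plan names.

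At stake are the precision and power of the time comparison, and whether the set of consultations behind it is fixed before anyone sees the times.

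**Working it through.** **Inputs** (Sample Size and Randomization): difference d = 30 s, SD σ = 90 s, α = .05, power 80%, 120 per group set for time, 400 per group enrolled.

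**Step 1. Reproduce the plan's figure.** For two independent means, n per group = 2 σ² (Zα + Zβ)² / d². Here σ²/d² = (90/30)² = 9.

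- One-sided, Zα = 1.645, Zβ = 0.84: 2 × 9 × (2.485)² = 111.15. This matches the printed figure.
- Two-sided, Zα = 1.96, Zβ = 0.8416: 2 × 9 × (2.8016)² = 141.3, so 142 per group. This does not match.

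The 111.15 therefore comes from a one-sided z.

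**Step 2. Power for the possible analysis sets.** Power = Φ(d / (σ √(1/n₁ + 1/n₂)) − Zα), with Zα = 1.96 two-sided or 1.645 one-sided.

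| AI / control | d / SE | Two-sided 5% | One-sided 5% |
|---|---|---|---|
| 120 / 120 | 30 / 11.62 = 2.582 | 73.3% | 82.6% |
| 400 / 120 | 30 / 9.37 = 3.203 | 89.3% | 94.0% |
| 400 / 400 | 30 / 6.36 = 4.714 | 99.7% | 99.9% |

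A noncentral t calculation gives 73.0% two-sided at 120 per group, in agreement with the first row.

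**Step 3. Precision.** The half-width of the 95% confidence interval is 1.96 × 90 × √(2/n): about 22.8 s at 120 per group and 12.5 s at 400 per group, against a target difference of 30 s.

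**Step 4. Separate the two issues.** Within the two-sided column, moving from 120 to 400 per group changes power from 73.3% to 99.7%; that is the effect of the unclear analysis set. Within the first row, moving from one-sided to two-sided changes power from 82.6% to 73.3%; that is the effect of the unstated sidedness. The shortfall below 80% arises only if both apply, that is, if 120 is the analysed number and the test is two-sided.

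**The case against.** The strongest reply is that 120 is simply the minimum for this objective. The sentence that follows it shares the consultations across both objectives and lets the larger number govern. No section orders a subsample or says that logged times will be dropped. Recording every control consultation to obtain typing time, and logging review time in every AI consultation, both fit an analysis of the full set. On that reading two-sided power is 99.7% and there is no power problem. The reply also notes that the study's expectations are directional, that on the one-sided basis actually used 120 per group gives 82.6%, and that 318 patients were enrolled by November 2024. If these were split evenly (an assumption), that is about 159 per group, already above 142.

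Much of this stands. A reader might infer a flat contradiction between the sample size section and Textbox 1. The text does not support that: 120 can be a minimum, and the phrase about analysing each recording individually can mean every recording or one recording at a time. A reader might also infer that data will be discarded or favourable recordings picked. That would require a subsample, which no section orders. Only AI-arm times are logged in the workflow; control times need manual listening, which could be a practical reason for a limit.

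What the reply does not remove is that the number is worded as the count to be analysed and is never restated once 400 per group is set. Nor does it supply the missing sidedness. The one-sided z has to be inferred from the arithmetic.

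**Conclusion.** The point holds as a lack of clarity on a main hypothesis, together with a sizing figure whose one-sided basis is not disclosed. If 120 per group is the analysed number and the test is two-sided at 5%, power for 30 s is about 73% and 142 per group would be needed for 80%. If the test is one-sided, 120 gives 82.6%. If all 400 per group are analysed, power is above 99% either way.

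It would go too far to conclude that the trial is underpowered for time saving: that needs both the narrower reading of the 120 and a two-sided test, and the article commits to neither.

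The figures assume an SD of 90 s in both arms and independent consultations. Limitations of the Study expects appreciable variation between professionals, which these figures ignore. They are also in seconds, whereas Statistical Analysis compares relative time in percent, so they do not carry over directly to the planned test.

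**What to change.** 1. State in Sample Size and Randomization that 120 per group is not a cap on the time analysis.
2. Analyse all AI consultations with a logged review time and all control recordings. If listening has to be limited, draw a random sample of control recordings within professional before any is timed, and compare it with all AI review times.
3. State whether the test is one- or two-sided. If two-sided, replace 111.15 and 120 by 142 per group as the required number.
4. Restate the power for the numbers actually used, on the scale actually analysed. Say that the present figures are in seconds and treat consultations as independent.

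The cost is a few sentences of protocol wording, to be settled before any control recording is timed. No extra listening is needed if 120 control recordings are kept: with 400 AI review times, two-sided power on the seconds scale is then about 89%. Listening hours rise only if all control recordings are timed, which one reading of Textbox 1 already implies.

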### Data Collection

The data collection process involves the following:

Satisfaction surveys completed by patients at the end of the consultation (with the AI-powered tool as a test and without the tool as a control). The survey will be given to the patient on paper by the health professional inside the doctor’s office at the end of the visit. They will be collected anonymously in a box upon exiting the office, in a visible and accessible place. This involves single-blinded data collection (the patient does not know whether the AI-powered tool is being used, although the health care professional does). These questionnaires will be available in Catalan and Spanish.Quality surveys at the end of each consultation by health care professionals, on a scale of 0-10 with the possibility of including open-ended comments, will be carried out directly through the AI-powered tool’s digital platform. These questionnaires will be available in Catalan and Spanish.Satisfaction surveys completed by health care professionals at the end of the study, as well as interviews to better understand the impact and limitations in a qualitative manner.Recordings of conversations between the patient and health care professional (Recog will delete the recordings at the end of the study).

These items align with study objectives and are detailed in the Multimedia Appendices 2 and 3.

Qualitative data will be collected using open-ended survey surveys for patients and health care professionals and structured interviews with professionals. These data will be analyzed using thematic analysis.

The study variables are mentioned in Textbox 1.

Study variables.
**Independent variables**
Indicator of whether the artificial intelligence (AI)–powered solution has been used in the consultation (no typing during the consultation; yes or no)Identifier of the health care professional involved (user code stored in the AI-powered tool)
**Dependent variables**
Results for each survey question, on a scale of 1-5.Time saved during consultations is measured by comparing the writing time in the 2 scenarios: one where doctors manually write notes during the consultation (non–AI-powered audios) and another where they review and correct notes generated by the AI-powered tool. For the non–AI-powered audios, investigators listen to the recordings and measure the exact time the professional spends writing. In AI-assisted consultations, the doctors use the platform to time their note corrections. By comparing these two measurements, the study aims to quantify the time-savings offered by the AI-powered tool, with each recording being analyzed individually for accuracy. This has been chosen because other forms of measurement (such as automatically measuring silences) may introduce greater biases (silences due to circumstances other than note taking) than human interpretation. Although logically it is not a perfect measure either, the savings impact is expected to be sufficiently significant for these random errors to have a very small impact in relative terms.In addition, health care professionals are asked to include, through the AI-powered tool’s digital platform, possibly relevant comments about the consultation they have just carried out, such as when a consultation has been carried out in multiple languages, with one participant speaking in Spanish and another in Catalan.

### Statistical Analysis

The main hypotheses of the study focus on evaluating the reported quality of care and saving time in the writing of clinical notes. To assess the improvement in reported quality of care, the normality of the sample will be checked using the Kolmogorov-Smirnov test with Lilliefors correction. Student *t* test for independent samples will be applied in the case of normality, or an equivalent nonparametric test otherwise. Key survey items, including patient-reported satisfaction with time spent, the attention received, and perceived care quality, as well as health care professional satisfaction with reduced administrative burden, ease of use, and note quality, will be analyzed to test for significant differences.

In terms of time savings, 2 aspects will be measured separately: the relative time (in percentage) that the professional spends writing notes during the consultation without using the AI-powered solution, and the relative time that the doctor spends reviewing the notes generated by the tool. Similarly, the normality of the sample will be checked using the Kolmogorov-Smirnov test with Lilliefors correction, and the Student *t* test or its nonparametric equivalent will be applied as appropriate.

Since the sample is not randomized, a sensitivity analysis will be conducted to account for potential selection bias. All statistical analyses will be performed using RStudio, considering a confidence level of 95% and a statistical power of 80%.

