**Methods:**

This proof-of-concept (PoC) study is conducted as a multicenter trial with the participation of several health care professionals (nurses and physicians) in primary care centers (CAPs). The key outcome measures include (1) patient-reported quality of care (evaluated through anonymous surveys), (2) health care professionals’ satisfaction with the care provided (assessed through surveys and structured interviews), and (3) time saved on clinical documentation (determined by comparing the time spent manually writing notes versus reviewing and correcting AI-generated notes). Statistical analyses will be performed for each objective, using independent sample comparison tests according to normality evaluated with the Kolmogorov-Smirnov test and Lilliefors correction. Stratified statistical tests will also be performed to consider the variance between professionals.

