### Limitations of the Study

One of the main limitations of this study is that the sample is not randomized, which may introduce selection bias. To address this, a sensitivity analysis will be performed to ensure that any potential bias is minimized. Related to the sample size, while substantial for a PoC study with 800 participants, may still be considered relatively small.

Another important limitation is the variability introduced by the participation of different health professionals, who can generate a significant variance in the results obtained, both in patient satisfaction and in the time saved in the consultation. Although patients were blinded to the use of the tool, their reported satisfaction may still be influenced by other factors such as the health care professional’s behavior or consultation dynamics. To mitigate this effect, it has been decided to involve a reasonable number of professionals, seeking a balance between reducing variance and avoiding an excessive burden on participants, although this will still be a limiting factor.

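### The main tests carry no term for the professional and hang on a normality check that 1-5 items cannot realistically pass; the stratified tests promised in the abstract are informational in the methods

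*Protocol article*

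**What the plan says.** All references are to the Protocol article.

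- **Main tests.** Statistical Analysis checks normality by Kolmogorov-Smirnov with Lilliefors correction. A Student t "test for independent samples will be applied in the case of normality, or an equivalent nonparametric test otherwise". The same rule applies to time, there expressed as a percentage. The nonparametric test is not named and no professional term appears.
- **Professional as a variable.** The independent variables include "Identifier of the health care professional involved (user code stored in the AI-powered tool".
- **Professional as a source of variance.** Limitations of the Study describes the professionals as people "who can generate a significant variance in the results obtained, both in patient satisfaction and in the time saved in the consultation".
- **Stratified tests.** Abstract, Methods: "Stratified statistical tests will also be performed to consider the variance between professionals". Sample Size and Randomization: "for information purposes the study also shows intermediate results stratified by type of consultation (first or follow-up) or by a health professional". Statistical Analysis does not mention them.
- **Allocation.** The Figure 1 steps alternate consecutive patients between arms and, in the same sentence, label this simple randomization. Statistical Analysis and Limitations say the sample is not randomized.
- **Sizing.** A mean difference under assumed normality: "σ=1 is estimated as an extreme case" and "d=0.25, as the minimum improvement we want to demonstrate" for satisfaction; SD 90 s and difference 30 s for time.

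**The concern.** When arms alternate within a professional, differences in level between professionals largely cancel from the arm comparison. An unpaired test still counts that variance in its standard error. The document names this variance and records the factor that would remove it, but leaves the factor out of the main tests and gives two different statuses to the analysis that would use it.

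The normality gate adds a second problem. A five-point item is not normal, and several hundred observations will show it. The t test assumed in the sizing then gives way to an unnamed test, and nothing in the section yields a difference in points or seconds. Yet the abstract's conclusions expect a saving of at least 30 seconds per visit, which is a statement about a mean.

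At stake are the precision of both main comparisons, whether their error rate is what it claims to be, and whether the reported result can be set against the effects the trial was sized for.

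**Working it through.** **1. The sizing contains no professional term.** The plan takes "standard values for α=.05 (95% confidence) and β=.8 (80% test strength) are selected". The printed figures come back as:

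- satisfaction: 4 × (1.645 + 0.84)² × 1² / 0.25² = 395.21
- time: 2 × (1.645 + 0.84)² × (90/30)² = 111.15

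Both are comparisons of two independent means with one-sided quantiles. The satisfaction figure is labelled per group but equals the total for both groups; the per-group value is 197.6 one-sided and 252 two-sided. That is a separate matter. Here it matters only that both figures rest on mean differences between independent observations.

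**2. The gate.** Lilliefors was applied to 300 simulated samples per setting, with four assumed five-point shapes (ceiling, moderate skew, uniform, rounded symmetric normal). Normality was rejected in 100% at n = 60, 120 and 400, in 94% to 100% at n = 30, and in 63% to 100% at n = 20. A mean of three symmetric items was rejected in 65% at n = 60, 99.7% at n = 120 and 100% at n = 400. At the planned size the t test is not reached for survey items; in small strata it might be.

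**3. Standard error with a common effect.** The document gives no ICC and no number of professionals, so both are assumed. With total SD 1 and n per arm:

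- unadjusted SE = √(2/n)
- true SE under balanced alternation = √(2(1 − ICC)/n)
- ratio = 1/√(1 − ICC)
- actual two-sided error = 2Φ(−1.96/√(1 − ICC))

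| ICC | SE too large by | Type I error | n per arm for 80% power, adjusted | Power at 400 per arm, unadjusted / adjusted (simulated) |
|---|---|---|---|---|
| 0.05 | 2.6% | 4.4% | 239 | 93.8% / 94.2% |
| 0.10 | 5.4% | 3.9% | 227 | 95.9% / 96.5% |
| 0.20 | 11.8% | 2.8% | 201 | 96.0% / 97.2% |
| 0.30 | 19.5% | 1.9% | 176 | 96.4% / 97.9% |

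Mann-Whitney behaved like the t test. For time at 120 per arm, two-sided power is 73.3% at ICC 0; with adjustment it is 75.5%, 77.7%, 82.3% and 87.0% at the four ICCs. Under genuine simple randomization the unadjusted test held 4.7% to 5.2% at every ICC and only lost efficiency.

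**4. Standard error when the effect varies.** Let the effect have SD τ over J professionals, with ICC 0.10 and 400 per arm. Then true SE = √(2 × 0.9/400 + τ²/J) = √(0.0045 + τ²/J), while the unadjusted SE stays near 0.071 to 0.072.

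| τ | J | True SE (formula) | Type I error of pooled t test (1,500 runs) |
|---|---|---|---|
| 0.2 | 10 | 0.0922 | 13.0% |
| 0.2 | 20 | 0.0806 | 8.2% |
| 0.3 | 10 | 0.1162 | 22.8% |
| 0.3 | 20 | 0.0949 | 14.3% |

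With τ = 0.1 and 10 or 20 professionals, the error was 5.9% and 4.9%. A professional intercept alone does not cure the inflation: at τ = 0.2 it gave 15%, 10% and 7% for 10, 20 and 40 professionals. A by-professional analysis held about 4% to 6%. If the target is the average effect among the participating professionals only, the pooled test stayed at 3.5% to 4.1%.

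**5. What the replacement test answers.** For satisfaction with a 0.25 shift at 400 per arm, power of t test and Mann-Whitney was 98.3% and 98.6%, 89.7% and 89.4%, 89.8% and 88.9% over three assumed shapes. For times, assuming log-normal data with equal means of 90 s and SDs of 90 against 45 to 60, Mann-Whitney rejected in 38% to 73% at 120 per arm. Welch's t test held 5% to 6%. With equal spread Mann-Whitney held about 4.5%.

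**The case against.** The other side has a good case on several points.

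- **The professional is not ignored.** The identifier is a listed variable, the abstract commits to stratified tests, and the limitations discuss the variance. A reader might infer that the study disregards the professional altogether; the document does not support that. The gap lies in the main tests and in the status of the stratified ones.
- **The pooled test mostly errs on the safe side.** A reader might infer an inflated false-positive rate. That needs an effect SD between professionals about as large as the whole 0.25-point target, and inference beyond the participating professionals. The article calls itself a proof of concept, but it also says the hypotheses are to be validated at a general level, so the wider target cannot be ruled out.
- **A gate that always fires does no shown harm to the satisfaction test.** No data-driven switching remains, and power and validity are close to those of the t test. This stands.
- **The 38% to 73% is not a type I error of Mann-Whitney.** The two distributions do differ. The figure also rests on assumed shapes and spreads, in seconds, whereas the analysis is in percentages. On that scale even the t test would not estimate 30 s. It shows only that a rank result cannot be read as a mean saving.
- **The survey code is unknown.** A reader might infer that stratified satisfaction tests are impossible. The text describes only a mark for tool use and transcription without identifying data, but the form is in an appendix not shown, and the collection box outside the office might identify the professional.

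What is left is what the article states: unadjusted main tests, a gate, and conflicting statements about the analysis by professional.

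**Conclusion.** The point holds in a limited form. The main tests omit a factor that is recorded, is named as a source of variance, and has the arms alternating within it. The abstract and the methods disagree on the status of the analysis that would use it.

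With a common effect under alternation the consequence is lost precision: a standard error about 3% to 20% too large for an assumed ICC of 0.05 to 0.30. At 400 per arm the power loss for 0.25 points is small, at most 1.5 percentage points in simulation, because power is already high. Under true simple randomization the error rate is right and only efficiency suffers. Anticonservative error of about 8% to 23% requires effect variation (assumed SD 0.2 to 0.3), 10 to 20 professionals, and inference to professionals in general; the document establishes none of the three as fact.

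The gate is a foregone conclusion for 1-5 items at the planned size. Its cost is interpretive: the usual rank test, itself an inference because the test is unnamed, does not estimate the 0.25-point or 30-second difference, and for times it can reject with equal means if spreads differ.

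**What to change.** 1. Make the main analysis of both outcomes professional-adjusted, with professional as a stratum or random intercept, and examine arm-by-professional variation. If the inference is to professionals in general, include a random arm effect. State which target is meant.
2. Drop the normality gate. Report the mean difference with 95% CI, and keep a stratified rank or ordinal analysis as a named sensitivity analysis.
3. Put the stratified analysis and its status in Statistical Analysis, so that it agrees with the abstract and with Sample Size and Randomization.
4. Reconcile the percentage of time in Statistical Analysis with the seconds used for sizing, and the alternation in the Figure 1 steps with the simple-randomization label.
5. If the anonymous survey form carries no professional code, add one to the remaining forms.

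The cost is wording plus, if needed, a code on the form. Forms already collected may lack the code (318 patients were enrolled by November 2024), and the interval may widen if effects differ by professional. A mixed model is one acceptable choice; a professional-stratified comparison would also honour the abstract's commitment.

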**Conclusions:**

We expect an improvement in the perceived quality of care reported by patients and a significant reduction in the time spent taking clinical notes, with a saving of at least 30 seconds per visit. Although a high quality of the notes generated is expected, it is uncertain whether a significant improvement over the control group, which is already expected to have high-quality notes, will be demonstrated.

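### The time-saving hypothesis is sized and forecast in seconds, but the only named test is on percentages whose denominator is not stated for the AI arm, so the test can mislead about seconds saved in either direction

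*Protocol article*

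**What the plan says.** All references are to the protocol article.

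- **Sample Size and Randomization** works in seconds: "σ=90 seconds and d=30 seconds, we obtain n=111.15 for each group". This is then set to "120 with the AI-powered tool and 120 without the tool". The 400 per arm needed for the satisfaction outcome will also serve the time outcome.
- **Abstract, Conclusions** forecasts a significant reduction in note-taking time, "with a saving of at least 30 seconds per visit".
- **Overview, Design, and Hypotheses of Study** sets typing time against review and correction time to find the size of the saving. **Dependent variables** says: "Time saved during consultations is measured by comparing the writing time in the 2 scenarios". **Limitations of the Study** describes the saving as a difference between two times.
- **Statistical Analysis** names the test (Student t or a nonparametric equivalent). It first defines the quantities as "the relative time (in percentage) that the professional spends writing notes during the consultation without using the AI-powered solution" and, for the AI arm, the relative time spent reviewing the generated notes. It gives no denominator for the second quantity.
- The workflow steps under Figure 1 place control-arm typing during the visit. In the AI arm, review comes after the doctor has said goodbye to the patient.

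**The concern.** Statistical Analysis names time saving as one of the main hypotheses. Its sample size and its forecast are in seconds, but its test is on shares. A share depends on its denominator as well as on documentation time.

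The denominator for review time is undefined. If it is visit length, or visit length plus review, it can differ between arms because of the tool. AI-arm professionals do not type during the visit, and the article hypothesises that they will interact more with the patient. A difference in percentages would then mix time saved with a change in visit length. At stake are a reported saving that is not one, a real saving that is missed, and a 30-second statement with no matching planned test.

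**Working it through.** **1. Reproduce the stated n.** The inputs from Sample Size and Randomization are σ = 90 s, d = 30 s and "standard values for α=.05 (95% confidence) and β=.8 (80% test strength) are selected" (β there denotes power). For two independent means:

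n per group = 2 × [σ(z_α + z_β)/d]²

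With one-sided z_α = 1.645 and z_β = 0.84: 2 × (90 × 2.485/30)² = 2 × 7.455² = 111.15, an exact match. Two-sided α = 0.05 gives 141.28. The figure is therefore for a difference in seconds, one-sided. Power for 30 s at 120 per group is 82.6% one-sided and 73.3% two-sided. At 400 per group it is above 99% either way.

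**2. Try to carry it to percentages.** This cannot be done, because the article gives no visit length and no SD in percentage points. For assumed visits, 30 s is 30/300 = 10.0 points (5 min), 30/600 = 5.0 (10 min), 30/900 = 3.3 (15 min) or 30/1200 = 2.5 (20 min).

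**3. Effect of the denominator (assumed visits).** Control: 600 s with 120 s typing, 120/600 = 20.0%.

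| AI arm | Share | Seconds saved |
|---|---|---|
| 120 s review, denominator 600 s | 20.0% | 0 |
| 120 s review, denominator 660 s | 18.2% | 0 |
| 120 s review, denominator 720 s (a longer visit, or 600 s plus review) | 16.7% | 0 |
| 120 s review, denominator 480 s (typing removed) | 25.0% | 0 |
| 90 s review, denominator 480 s | 18.75% | 30 |
| 90 s review, denominator 480 + 90 = 570 s | 15.8% | 30 |

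Zero seconds saved can appear as a gain of 3.3 points or a loss of 5.0. A 30 s saving can appear as 1.25 or 4.2 points.

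**4. Effect on the test (simulation, assumed inputs).** Control documentation has mean 150 s and SD 90 s, and the control visit averages 600 s. Each scenario has 1,500 runs of a two-sided t test at 0.05. Each cell gives 120 / 400 per group.

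| Scenario | Percentage test | Test in seconds |
|---|---|---|
| No saving; review added to an unchanged visit | saving declared 93.1% / 100% | 2.7% / 2.7% |
| No saving; AI denominator 60 s longer | saving declared 33.7% / 82.5% | 2.2% / 2.3% |
| No saving; AI denominator 120 s longer | saving declared 83.2% / 100% | 3.1% / 2.7% |
| 30 s saved; visit unchanged, review outside it | saving declared 31.5% / 71.5% | 73.3% / 99.9% |
| 30 s saved; visit shorter by the typing time, review outside it | saving declared 0% / 0%; loss declared 51.1% / 97.9% | saving declared 74.1% / 99.7% |
| 30 s saved; denominator built the same way in both arms (consultation plus documentation) | saving declared 70.1% / 99.5% | 71.9% / 99.5% |

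The last row shows that the percentage is not wrong in itself. It agrees with seconds when the denominator is built alike in both arms and the rest of the visit does not change.

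**5. What a claim of 30 s or more requires.** The planned n is for a test against zero. If the lower 95% limit must reach 30 s, 80% power needs a true saving of 30 + (1.96 + 0.842) × SE, where SE = 90 × √(2/n).

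- n = 400: SE = 6.36 s; 30 + 2.802 × 6.36 = 47.8, about 48 s.
- n = 120: SE = 11.62 s; 30 + 2.802 × 11.62 = 62.6, about 63 s.

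If the true saving is exactly 30 s, the lower limit reaches 30 s in only about 2.5% of trials.

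**The case against.** - **The article does not abandon absolute time.** A reader might infer that the hypothesis in seconds is never tested. That goes too far. Study Objectives promises statistical tests comparing consultations with and without the tool, and three other sections describe comparing times. What stands is that the only section naming the test names it for relative times.
- **The denominator is an assumption.** A reader might take it to be consultation duration, with review necessarily outside it. The article does not say so, and visit plus review is equally possible. A condensed article may leave the exact definition to a fuller document. The conflict of scale remains, because the article itself states both scales.
- **The error need not favour the tool.** A reader might infer that the percentage test inflates the benefit. The calculations show that it can also hide a real saving. A lower share at equal seconds is a true statement about share and misleads only if reported as time saved.
- **The 30 seconds in the Abstract is an expectation**, not a success criterion, and the main-text Conclusion gives no such figure. This stands.
- **The examples rest on assumed visit lengths.** This also stands: they show what is possible, not what is likely.

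**Conclusion.** The point holds as a contradiction of scale on a main hypothesis: seconds in the sample size and the forecast, percentages in the named test, and no stated denominator for review time. The 111.15 per group does not support a test on percentages. The possible distortion is large. Under the assumed inputs, with no seconds saved, the percentage test declares a saving in 34% to 93% of trials at 120 per group when the AI denominator is longer. It finds no saving at all when 30 s is saved and the visit shortens by the typing time. The larger sample of 400 per group does not protect against this and makes a wrong answer more certain. These sizes depend on the assumed visit lengths, on SD 90 s and on the undefined denominator, so neither the direction nor the size of error in this trial can be predicted. Nothing is lost beyond repair, since times are recorded in both arms.

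**What to change.** In Statistical Analysis, make documentation time in seconds per consultation the tested outcome for the time hypothesis. Report the mean difference (control minus AI) with its 95% CI, whichever test the normality check selects. This matches the sample size.

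Keep the percentage as a secondary descriptive result, with one denominator definition written down for both arms. Report visit duration by arm beside it.

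Word the conclusion as the estimated saving with its CI. State a saving of 30 seconds or more only if the lower confidence limit is 30 s or higher, and say that the trial was sized for a test against zero.

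**Cost.** The change of scale is a change of wording. Control typing time is measured from the recordings, and review time comes from the start and finish clicks. Visit duration should be taken from the recordings before their planned deletion at the end of the study. On the article's timeline, analysis follows recruitment, so the text can be settled first. The stricter 30-second claim does have a price: a true saving of about 48 s for 80% power at 400 per group, or about 63 s at 120 per group, with SD 90 s.
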